### 2.2. Intervention Protocol

The intervention sessions will be held at the patient’s home. If this is not possible, they will be carried out in the research laboratory of the Beata María Ana Hospital or in the Parkinson’s patients association or current attending hospital of the patient.

Depending on the assignment to each of the experimental groups, the patients will undergo neurorehabilitation of cognitive functions or will not receive any therapy.

Due to the characteristics of the study, all participants will know the experimental group to which they belong. The researcher evaluating the preintervention and postintervention balance is blinded to the experimental group.

Control Group: The control group will not receive any therapy. They will be simply evaluated at the same time as the experimental group.

Experimental Group: In the experimental group, patients will receive a 12-session neuropsychological rehabilitation protocol that will be carried out over four weeks (3 weekly sessions). The protocol and the number of sessions has been designed by neuropsychologists following the Díez-Cirarda et al. recommendations [24] (Figure 1 and Figure 2).

Each session will consist of a series of cognitive stimulation tasks aimed at improving attention, perception, and processing speed. These tasks will be applied through the NeuronUp (Neuronup SI, La Rioja, Spain) cognitive neurorehabilitation platform to achieve maximum homogeneity and objectivity in their application. The protocol is preprogrammed in the application and is identical for all patients. Performing tasks through the platform allows one to objectively record the performance of each patient in all tasks to ensure adherence and efficacy. Before the first session, a training session will be carried out under the supervision of a researcher. All doubts that may arise will be resolved.

The NeuronUp (Neuronup SI, La Rioja, Spain) cognitive neurorehabilitation platform has a home activities module. In this case, the tasks and the days of their completion will be assigned, and the patient has to access the platform in a computer connected to internet to perform the intervention. The program has a direct researcher–patient feedback tool, in which the intervention and evolution of the patient can be followed in real time, being able to adjust the contents in the same way as in person. The researcher will be in direct contact with the patient and will remind the patient of the day and time at which he should carry out the session and will check at the end of the session that it has been carried out successfully.

During the intervention, the subjects will be seated in a relaxed position in front of the computer. No adverse effects are expected, in case of occurrence, mild adverse effects due to the use of the computer such as dizziness, mental fatigue, headaches, or other will be evaluated after each session if they persist, they will be notified to a licensed physician who can decide the management of the patient.

### 2.3. Outcomes Measurement

All detailed measures will be evaluated in the two groups before and after the intervention. To ensure that all patients are in the “ON” state, the evaluation and intervention will take place one hour after taking the dopaminergic medication and UPDRS III [25] will be recorded before the measurements.

The evaluation prior to the intervention will be carried out in a single session on the Thursday or Friday before the start of the intervention and the subsequent one, on Monday or Tuesday after the end of the intervention. Necessary breaks can be taken to avoid patient fatigue (Figure 2).

#### 2.3.1. Main Outcomes

##### Instrumental Stability Evaluation

Objective metrics using the Biodex Biosway portable balance system [26] (Biodex, Version 1.08, Biodex, Inc., Shirley, NY, USA) that allows one to determine the following determinations:

1. Stability limits test: This test is a good indicator of dynamic stability control with a normalized balance of improvement [27]. The patient shifts its weight over a platform to control the cursor displacement in order to reach targets in a screen. The position of the objectives has been pre-established by the manufacturer at 50% of the stability limits according to the height of each volunteer. The test dependent variables provided by the machine are the time (seconds) it takes for the subject to complete the test and the directional control value, which is the proportion of the distance travelled by the cursor from the center to each target (based on that 100% is a straight line from the center to the intended target). This means that the greater the distance travelled by the subject, the worse their stability.

2. Fall risk test: The test protocol is incorporated in this system and normative data is used to assess the risk of falls for the subjects.

##### Clinical Stability Evaluation

*Berg Balance scale*

The Berg balance scale (BBS) is designed to measure changes in functional standing balance over time. This scale measures the balance skills observed during tasks that involve sitting, standing, and changing positions. Total scores are indicative of general balance skills [28].

*Timed stand up and go test*

The timed “Up and Go” test [29] is a common mobility measure in rehabilitation. This test measures parameters such as turning, sitting, and walking speed. The mean angular velocity during turning and the duration of the turning and sitting phase have been shown as valid measures of balance in PD and are also responsive to rehabilitation [30,31].

##### Neurocognitive Evaluation

A protocol designed to measure processing speed, sustained and alternating attention, working memory, interference control, visual search, and verbal fluency (Stroop test [32,33,34], Trail Making Test [35,36], WAIS-III Processing Speed-Digit Symbol Coding, Processing Speed-Symbol Search, Digit Span [37], FAS Word Fluency [38], and The Bells Test [39]) will be administered by a neuropsychologist ([name]) experienced in their application in order to evaluate the efficacy of the rehabilitation protocol.

##### Computerized Reaction Times Battery

Reaction time tests are a predesigned set of computerized tasks to objectively measure various cognitive domains such as perception and alertness, inhibition, and visual search. The system has been described in and published in Arroyo et al. [40].

#### 2.3.2. Secondary Outcomes

*Parkinson’s Disease Questionnaire 39* (PDQ39) [41]: It is a specific questionnaire for evaluating the quality of life of Parkinson’s patients. The quality of life of patients with PD is associated with the subject’s perception of their gait and balance. The improvement in mobility and balance is related to the improvement in the PDQ-39 scores, especially in the set of items that measure mobility (items 1–10) [42].

##### Neurophysiological Evaluation

The balance is related to an increase in theta power in the frontal, central, and parietal regions. Increased theta power in these zones correlates with better balance performance [43].

A resting state 64 electrodes EEG recording will be performed using the actiCHamp amplifier (Brain Vision LLC., Morrisville, NC, USA) with Ag/AgCl active scalp electrodes (actiCAP electrodes, Brain Vision LLC., Morrisville, NC, USA), acquisition will be carried out using NeuroRT Studio software (Mensia Technologies SA, Paris, France). The EEG signal processing procedure will be performed using MATLAB functions (MathWorks Inc., Natick, MA, USA), specifically the EEGLab toolbox. The spectral entropy correlation, the coherence, and the differences of interhemispheric divergence between the experimental group and the controls will be analyzed as results.

### 2.4. Data Analyses

The SPSS software package (version 25.00; SPSS Inc., Chicago, IL, USA; IBM, New York, NY, USA) will be used by a blinded statistician for statistical analysis of the data. Demographic and clinical variables will be presented as mean and standard deviation. A 95% confidence interval (CI) will be taken, considering statistically significant all those values that had a *p* < 0.05. Parametric statistical tests will be used for hypothesis testing (*n* > 30). To show the differences in the variables, a 2 × 2 analysis of variance (ANOVA) of repeated measures will be carried out, taking time and group as factors, being the control and experimental groups and the pretreatment and posttreatment time measures. If significant differences are found in any of the interactions, a post hoc analysis with Bonferroni correction will be performed. The effect sizes will be calculated using Cohen’s d, classifying them into small (d between 0.20 and 0.49), medium (d between 0.50 and 0.79), or large (d greater than 0.80) following Cohen’s method.

Possible confounders or mediating variables will be included as covariates in the analysis.

For the rest of the variables, a Pearson correlation or linear regression will be carried out with the motor and balance variables. The low correlation will be that with values between 0.2 and 0.39; the correlation will be considered moderate when the value goes from 0.40 to 0.79; and high when the correlation value is greater than 0.80.

For the EEG entropy analysis, nonparametric Kruskal–Wallis (KW) tests will be performed to compare the distributions, the Mann–Whitney U test to evaluate the difference between the median values, and the Wilcoxon rank sum test for measure pre/post intervention changes, with a significance level of 0.05 and the alternative hypothesis of unequal values. Therefore, small *p*-values will suggest significant differences between populations.

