### 2.1. Study Design and Participants

The participants will be recruited in PD outpatient’s clinic of the Beata María Ana Hospital of Madrid and referred from other collaborators centers and hospitals or self-referrals that know the research project due to the dissemination through social networks. The subjects included will be assessed by a neurologist expert in movement disorders ([name])) (Figure 1). All patients will be idiopathic PD patients diagnosed according to the UK Parkinson’s Disease Society Brain Bank criteria. The inclusion and exclusion criteria are shown in Table 1. During the protocol, changes in dopaminergic medication will be prohibited and, if necessary, will lead to the exclusion of the patient. The total daily dose of dopaminergic drugs will be recorded and controlled in the final analysis of the results.

To control the Wearing-off effect, a specific questionnaire will be applied both at the beginning and at the end of the study [23].

The data will be anonymized and will be recorded separately, being safeguarded in accordance with current European data protection laws. All data will be recorded and verified twice in a database designed for the study.

The study design will be a parallel, randomized and controlled experimental study. The patients included in the sample will be divided into two groups: Cognitive rehabilitation (experimental) and no therapy (control). The distribution will be random, but it will be ensured that there is an equitable number of subjects in each of the stages of the disease, being matched by their score in HY. The randomization of the sample will be done through the website: http://www.randomization.com/ (accessed on 12 February 2020). The duration of the study will be 18 months.

The sample will be composed of 46 patients randomly distributed in a 1:1 ratio (Figure 1). To calculate the sample size, we used the GRANMO calculator. Accepting an alpha risk of 0.05 and a beta risk of 0.2 in a one-sided contrast, 23 subjects are required to detect a difference equal to 12 points in the Biodex objective stability limits test assessment (Biodex, Version 1.08, Biodex, Inc., Shirley, NY, USA). The standard deviation in the stability limits test obtained in our sample from the NeuroMOD project was 16.16. Considering a 15% loss, it will be necessary to reach a sample of 26 patients in each group.

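### At least five balance variables share main-outcome status with none named primary and no adjustment across them, so the postural-stability hypothesis lacks 5% error control

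*Protocol article*

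**What the plan says.** The Introduction gives one main hypothesis, that postural stability improves with cognitive rehabilitation compared with no therapy, and treats it as something the trial can confirm.

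Section 2.3.1 (Main Outcomes) lists the stability limits test, the fall risk test, the Berg scale, the timed Up and Go, seven neuropsychological tests and a computerised reaction-time battery. The stability limits test yields two results: "The test dependent variables provided by the machine are the time (seconds"), and directional control, which is a proportion with 100% as the ideal. The cognitive tests are given "in order to evaluate the efficacy of the rehabilitation protocol". None of these measures is called primary. Only quality of life and EEG fall under secondary outcomes.

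Section 2.1 sizes the trial on one test: "Accepting an alpha risk of 0.05 and a beta risk of 0.2 in a one-sided contrast, 23 subjects are required". The purpose of that number is given as "to detect a difference equal to 12 points in the Biodex objective stability limits test assessment". It adds: "The standard deviation in the stability limits test obtained in our sample from the NeuroMOD project was 16.16". It does not say which of the test's two variables is meant.

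Section 2.4 specifies a 2 × 2 "analysis of variance (ANOVA) of repeated measures will be carried out, taking time and group as factors". On significance it says "A 95% confidence interval (CI) will be taken, considering statistically significant all those values" with p below 0.05. On multiplicity it says only: "If significant differences are found in any of the interactions, a post hoc analysis with Bonferroni correction will be performed". It then relates the remaining variables to the motor and balance measures by correlation or regression.

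**The concern.** A confirmatory claim needs one designated test, or a rule for combining several, so that the chance of a false claim is known in advance. Here the claim concerns postural stability. At least five variables measure it with equal standing, and each has its own 0.05 threshold. The Bonferroni step works within the analysis of a single variable once its interaction is significant, so it offers no protection across variables. The sample size paragraph points to the stability limits test, but neither section 2.3.1 nor section 2.4 ranks that test above the others.

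At stake is how the result will be read. If one balance variable out of five is significant, the plan gives no basis for saying whether the hypothesis has been confirmed.

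**Working it through.** **The plan's own figure.** Inputs from section 2.1: difference 12, SD 16.16, one-sided alpha 0.05, power 80%.

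n per arm = 2 × [16.16 × (1.645 + 0.842) / 12]² = 22.4, rounded up to 23. This matches the stated 23, so the sizing is for one variable tested once.

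**Count of main outcomes (section 2.3.1).**
- Balance: stability limits time, directional control, fall risk, Berg, Up and Go = 5. Up and Go is counted once, although several components are described.
- Cognitive: Stroop, Trail Making, Digit Symbol Coding, Symbol Search, Digit Span, FAS, Bells = 7.
- Reaction-time battery, counted once = 1.
- Total = 13.

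**Formulas under independence.** For k tests at two-sided 0.05:
- at least one false positive in either direction: 1 − 0.95^k
- at least one favouring treatment: 1 − 0.975^k

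For k = 5: 1 − 0.95^5 = 0.226 and 1 − 0.975^5 = 0.119. For k = 13: 1 − 0.95^13 = 0.487 and 1 − 0.975^13 = 0.280.

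**With correlation.** The documents give no correlations between outcomes. A common correlation r of 0.3 to 0.8 is therefore assumed, with all variables oriented so that higher is better. The rates come from simulated equicorrelated normal test statistics (400,000 draws, cut-off 1.96).

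| Variables tested | Either direction: independent | Either direction: r = 0.3 to 0.8 | Favouring treatment: independent | Favouring treatment: r = 0.3 to 0.8 |
|---|---|---|---|---|
| 1 | 5% | – | 2.5% | – |
| 2 (stability limits only) | 9.8% | 9.5% to 7.8% | 4.9% | 4.8% to 3.9% |
| 5 (balance) | 22.6% | 20.9% to 12.7% | 11.9% | 10.5% to 6.3% |
| 13 (all, if each is tested) | 48.7% | 41.9% to 19.2% | 28.0% | 21.3% to 9.6% |

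The columns favouring treatment assume the two-sided test that the ANOVA F test implies. If the one-sided 0.05 used for sizing were applied to each variable instead, the five-variable figure favouring treatment would be 1 − 0.95^5 = 22.6% under independence.

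**The case against.** Several points on the other side have force.

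- **Number of tests.** A reader might infer that a dozen or more outcomes are each compared between groups at 0.05. The text does not establish this. Section 2.4 sends the rest of the variables to correlation or regression with the balance measures, and a natural reading reserves the ANOVA for balance and motor variables. The 13-outcome figures are therefore conditional.
- **Which claim.** The Introduction separates postural stability from the neuropsychological evaluation and attaches the main hypothesis only to the first. A chance finding on a cognitive test cannot confirm a balance hypothesis, so 49% is not the error rate of the central claim.
- **Direction.** The hypothesis is that balance improves. A significant result favouring control would not confirm it, so 12% is the fairer independence figure under two-sided testing, with 23% covering either direction.
- **No stated decision rule.** The article does not say that one significant balance variable is enough. It sets a threshold and leaves open how several results are to be combined.
- **The sized variable.** One of the two stability limits variables is in seconds and the other is a percentage, so 12 points most naturally means directional control.
- **Scope.** The article is condensed, and testing order or a choice such as Holm can properly be left to the analysis plan.

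These points narrow the concern without removing it. On the narrowest count, five balance variables still share main status under one unadjusted threshold. The absence of a decision rule is part of the problem. The choice of primary endpoint belongs in the protocol. The article makes its choice by giving all these measures the same rank, so this is not a detail left for later.

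**Conclusion.** The point holds for the balance claim. As written, the plan does not hold the error rate of its main hypothesis at 5%. If any significant balance variable were taken as support, the chance of at least one false positive would be about 23% in either direction under independence, or about 12% in favour of treatment against 2.5% for a single test. For assumed correlations of 0.3 to 0.8 these fall to about 21% to 13% and 11% to 6%, still above the single-test rates.

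Only if each cognitive measure also gets its own ANOVA does the figure reach about 49% over 13 outcomes under independence, or roughly 42% to 19% for the same correlations. A reader might conclude that a chance positive is likely. The documents do not support that wording: no balance-only figure approaches even odds, and the 13-outcome figure comes near it only if all 13 are tested and independent. Counting further scores per test would raise the numbers, but the article does not say which scores will be analysed.

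**What to change.** Name one primary endpoint in section 2.3.1: the stability limits variable on which the trial was sized, tested by the group-by-time effect. This appears to be directional control. The sponsor should confirm that both the 12 points and the SD of 16.16 refer to it and state this in section 2.1. Reclassify every other measure in section 2.3.1 as secondary, reported with estimates and confidence intervals as supportive evidence. Section 2.4 should say that the main hypothesis is judged on the primary endpoint alone. Any ordered or adjusted testing of secondary measures can be left to the analysis plan.

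The cost is wording in the protocol and matching text in the registration, with no added patients, visits or measurements. The price is that the other balance and cognitive measures can no longer confirm the main hypothesis on their own. Keeping several co-equal outcomes would cost more. At 23 per arm, Bonferroni over five variables (one-sided 0.05/5 = 0.01) takes power for the 12-point difference from Φ(2.518 − 1.645) = 81% to Φ(2.518 − 2.326) = 58%, where 2.518 = 12 / (16.16 × √(2/23)).

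### The EEG entropy plan names the Wilcoxon rank sum test, an independent-samples test, for pre/post changes that are paired

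*Protocol article*

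**What the plan says.** Section 2.4 (Data Analyses) gives EEG entropy its own nonparametric plan, with three tests for three tasks:

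- Kruskal–Wallis: "For the EEG entropy analysis, nonparametric Kruskal–Wallis (KW) tests will be performed to compare the distributions".
- Mann–Whitney: "the Mann–Whitney U test to evaluate the difference between the median values".
- Wilcoxon rank sum: "the Wilcoxon rank sum test for measure pre/post intervention changes".

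All are run "with a significance level of 0.05 and the alternative hypothesis of unequal values", that is, two-sided at 5%.

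Section 2.3 (Outcomes Measurement) fixes the data structure: "All detailed measures will be evaluated in the two groups before and after the intervention". Each patient therefore contributes a pre value and a post value. The Wilcoxon signed-rank test is not named anywhere in the article. EEG appears under Secondary Outcomes, and its section says that differences between the experimental group and the controls will be analysed.

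**The concern.** The rank sum test takes its null distribution from two samples that are independent of each other. Pre and post values from one patient are not. When they are positively correlated, the test overstates the sampling variation of the pre/post difference, so its p-values are too large and real changes are missed. When they are negatively correlated, it rejects too often.

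This is not a detail left to an analysis plan that is not shown. The article names a specific test, and on the plain reading it is the wrong one. Rank sum and Mann–Whitney U are two names for one procedure, so the list gives two tasks to the same test and leaves the paired task without a suitable one. A statistician who followed the text literally would run an unpaired test on paired data.

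**Working it through.** **Inputs.**

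- Level and sidedness: 0.05, two-sided (section 2.4, EEG sentence).
- Pairing: the same patients before and after (section 2.3).
- Number of pairs: 23, from section 2.1: "Accepting an alpha risk of 0.05 and a beta risk of 0.2 in a one-sided contrast, 23 subjects are required". Running the pre/post test within one arm is an assumption; section 2.4 does not say so.
- Pre/post correlation r, EEG SD and EEG effect: not given. The value of r is therefore an assumed range, and the effect is an assumed shift of 0.5 SD.

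**The plan's own figure.** The 23 per arm is for the Biodex stability limits test: 2 × (1.645 + 0.842)² × 16.16² / 12² = 2 × 6.18 × 261.15 / 144 = 22.4, rounded up to 23. It reproduces. No sample size or power is stated for EEG, so 23 serves here only as the number of pairs.

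**Step 1: same test, two names.** On one simulated data set of two samples of 23, the rank sum and Mann–Whitney tests returned the same p-value, 0.1838.

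**Step 2: true size, large-sample approximation.** An unpaired test assumes variance 2σ²/n for the pre/post difference; the true variance is 2σ²(1 − r)/n. The true size of the nominal 5% test is then about 2 × [1 − Φ(1.96/√(1 − r))], whatever n is:

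- r = 0: 1.96/1 = 1.96, size 5.0%
- r = 0.3: 1.96/0.837 = 2.34, size 1.9%
- r = 0.5: 1.96/0.707 = 2.77, size 0.6%
- r = 0.7: 1.96/0.548 = 3.58, size 0.03%

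**Step 3: simulation at 23 pairs.** Bivariate normal data, 20,000 replicates per setting, both tests applied to the same pairs.

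| r | Size, rank sum | Size, signed-rank | Power at 0.5 SD, rank sum | Power at 0.5 SD, signed-rank |
|---|---|---|---|---|
| −0.3 | 0.084 | 0.049 | 0.38 | 0.28 |
| 0 | 0.049 | 0.048 | 0.37 | 0.35 |
| 0.3 | 0.021 | 0.046 | 0.34 | 0.47 |
| 0.5 | 0.008 | 0.049 | 0.32 | 0.60 |
| 0.7 | 0.001 | 0.048 | 0.30 | 0.82 |

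Repeat runs moved the power entries by no more than 0.02 (for example 0.45 for signed-rank at r = 0.3, and 0.31 vs 0.84 at r = 0.7) and gave rank sum sizes of 0.024, 0.010 and 0.001 at r = 0.3, 0.5 and 0.7. The signed-rank test stays close to 5% throughout.

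**Step 4: share of power lost.** At shifts chosen so that signed-rank power is about 0.76, rank sum power is 0.65 (r = 0.3), 0.49 (r = 0.5), 0.38 (r = 0.6) and 0.24 (r = 0.7). The loss is 1 − 0.65/0.76 = 14%, 1 − 0.49/0.76 = 36%, 1 − 0.38/0.76 = 50% and 1 − 0.24/0.76 = 68%. At r = 0 there is none. With the 26 per group that section 2.1 also mentions, the pattern is the same (0.49 vs 0.77 at r = 0.5).

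**Step 5: the other reading.** A rank sum test comparing post-minus-pre change scores between the two arms is valid: its simulated size was 0.051 at r = 0.5 and 0.050 at r = 0.8.

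**The case against.** The best defence is that the wording allows a valid analysis. A rank sum test for changes could mean a between-arm comparison of each patient's change score, and the EEG section does describe its results as differences between the experimental group and the controls. Step 5 shows that this version holds its level. The possibility stands, but it is the less likely reading: Mann–Whitney U, the same test, is already listed for a separate task, which points to a misnamed signed-rank test. Either way the sentence needs correcting, because the text does not say which is meant.

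Four stronger readings are tempting, and the documents do not support them.

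- *Most of the power is lost.* That depends on r, which the article does not give. At the shifts in step 4, half the power is lost only at r of about 0.6, and none at r = 0.
- *One test is named three times and Kruskal–Wallis should go.* The article does not say how many distributions Kruskal–Wallis compares. If there are two, the redundancy does no harm.
- *The trial's main conclusion is at risk.* The sentence covers EEG entropy only. The balance outcomes have a 2 × 2 repeated-measures ANOVA with time and group as factors, which respects the pairing.
- *Theta power should be an analysed outcome because "Increased theta power in these zones correlates with better balance performance".* That is a separate choice of outcome and has no bearing on which test suits paired data.

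**Conclusion.** The sentence is wrong as written, with moderate severity, and the error is confined to the secondary EEG entropy analysis. Used on pre versus post values, the named test is miscalibrated at any non-zero correlation. It is conservative if r is positive (true size from about 2% at r = 0.3 down to 0.1% at r = 0.7) and too liberal if r is negative (about 8% at r = −0.3). The direction and the need for a paired test follow from the article alone. The sizes rest on assumed correlations, normal data, 23 pairs within one arm and, for the power figures in the table, a 0.5 SD shift, so they should be quoted as a range.

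**What to change.** In section 2.4, replace the rank sum clause with two statements. First, within-arm pre/post change in EEG entropy is tested with the Wilcoxon signed-rank test and reported descriptively, since change within one arm does not show a treatment effect. Second, the between-arm comparison is the Mann–Whitney U (rank sum) test on each patient's post-minus-pre change. If the authors meant the change-score comparison all along, the second statement makes that plain.

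The cost is about one sentence of analysis wording. It needs no new data, no change in sample size, and no change to the balance analyses.

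### The EEG entropy pre/post change is assigned the Wilcoxon rank-sum test, an independent-samples test that ignores the pairing of each patient's two recordings

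*Protocol article*

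**What the plan says.** Section 2.4 of the protocol article gives EEG entropy three nonparametric procedures: Kruskal–Wallis to compare distributions, "the Mann–Whitney U test to evaluate the difference between the median values", and "the Wilcoxon rank sum test for measure pre/post intervention changes". All are to be run "with a significance level of 0.05 and the alternative hypothesis of unequal values", that is, two-sided.

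On the data, section 2.3 states: "All detailed measures will be evaluated in the two groups before and after the intervention". EEG is listed under secondary outcomes in section 2.3.2, where the results of interest are differences between the experimental group and the controls.

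The document names no paired nonparametric test, such as the Wilcoxon signed-rank test. The repeated-measures ANOVA in section 2.4 does treat time as a within-patient factor, but EEG entropy has its own paragraph with the tests above.

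**The concern.** Two recordings from one patient are not two independent observations. The rank-sum test takes its null distribution from independent samples, so on raw pre and post values it measures the shift against the spread between patients rather than the spread of the within-patient differences. When the recordings are positively correlated, that error term is too large and the p-value is too large with it.

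The wording also gives one procedure two names and two jobs, because the Wilcoxon rank-sum test and the Mann–Whitney U test are the same test. An analyst who follows the plan literally runs an unsuitable test. One who quietly substitutes the signed-rank test departs from the published plan. At stake is whether a within-patient change in EEG entropy is detected, and whether the plan defines an EEG comparison between the randomised arms at all.

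**Working it through.** **Inputs**
- Patients per arm: 23. Section 2.1 says "23 subjects are required to detect a difference equal to 12 points in the Biodex objective stability limits test assessment" and "The sample will be composed of 46 patients randomly distributed in a 1:1 ratio".
- Two-sided level for EEG tests: 0.05 (section 2.4).
- Pre/post correlation r of EEG entropy: not given. Assumed 0.3 to 0.8, with 0 and −0.3 as checks.
- True change: not given. Assumed 0.5 SD, with 0.8 SD as a second case.
- Data: assumed bivariate normal with equal SDs.

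**The plan's own figure.** The 23 reproduces from section 2.1 (difference 12, SD 16.16, one-sided alpha 0.05, power 0.80):

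n = 2 × 16.16² × (1.645 + 0.842)² / 12² = 2 × 261.15 × 6.18 / 144 ≈ 22.4, rounded up to 23.

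This figure was set for the Biodex stability limits test and serves here only as the number of pairs in one arm.

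**Hand check of size.** An independent-samples test takes the variance of the pre/post difference in means as 2σ²/n. With pairing it is 2σ²(1 − r)/n. The test statistic under no change therefore has SD of about √(1 − r) instead of 1, and the true size is about 2 × [1 − Φ(1.96/√(1 − r))]:
- r = 0: 1.96/1 = 1.96, size 0.050
- r = 0.3: 1.96/0.837 = 2.34, size 0.019
- r = 0.5: 1.96/0.707 = 2.77, size 0.006
- r = 0.7: 1.96/0.548 = 3.58, size 0.0003

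This is the argument for means; ranks behave similarly, as the simulations show.

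**Simulation.** Rank-sum was applied to pre versus post values and signed-rank to the differences, both at two-sided 0.05. Ranges cover repeated runs of 4,000 to 20,000 datasets per setting. With 23 pairs and a change of 0.5 SD:

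| r | Size, rank-sum | Power, rank-sum | Power, signed-rank |
|---|---|---|---|
| 0.3 | 0.020–0.021 | 33–34% | 46–47% |
| 0.5 | 0.007–0.008 | 31–32% | 60–62% |
| 0.7 | 0.001–0.002 | 28–30% | 82–83% |
| 0.8 | below 0.001 | 27% | 94% |

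The signed-rank size stayed between 0.047 and 0.052 throughout. At r = 0 both tests hold their level (0.048 and 0.049). At r = −0.3 rank-sum is anti-conservative, at 0.079.

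**How far the power loss depends on the assumptions** (rank-sum versus signed-rank):
- Change of 0.8 SD, 23 pairs: 76–77% versus 86–87% at r = 0.3; 80–81% versus 94–95% at r = 0.5; 84–85% versus 99% or more at r = 0.7.
- Change of 0.5 SD, both arms pooled (46 pairs): 65–66% versus 78% at r = 0.3; 69% versus 90% at r = 0.5; 73% versus 99% at r = 0.7.

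**The valid use.** Rank-sum comparing two independent groups of 23, which is the situation when per-patient changes are compared between arms, has simulated size 0.044 to 0.051.

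**The case against.** The best defence is that the sentence can be read validly. The Mann–Whitney clause names no groups, the rank-sum clause speaks of changes, section 2.3.2 frames the EEG results as differences between arms, and the EEG paragraph closes by speaking of differences between populations. Rank-sum on per-patient changes compared between arms would fit. This reading is possible, so it would go too far to say the p-value is wrong whatever the authors meant. But the text does not state it, and it would make the clause a second Mann–Whitney test under another name.

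A second defence is that this is a slip for signed-rank. Naming Wilcoxon separately for pre/post change, next to a repeated-measures ANOVA, points that way. If so, the harm occurs only if the slip is carried into the analysis. The published text still names the wrong test.

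A reader might also infer that the test loses most of its power, or that a real EEG change would usually be reported as absent. The documents give neither the correlation nor the expected change, so they do not support this in general. At 0.5 SD and r = 0.3 about a quarter of the power is lost, and the signed-rank test would itself miss that change more often than not. At 0.8 SD, or with the arms pooled, rank-sum finds the change in most trials. Nor is there a route to a false claim of benefit under positive correlation, where the error is conservative.

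Finally, the reach is narrow. The clause concerns EEG entropy, a secondary outcome, and a within-arm test is not the randomised comparison in any case. All of this limits the size of the point; none of it makes the named test suitable for paired values.

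**Conclusion.** The point holds as a wrong test for its plain purpose, with limited consequences. Read as a comparison of pre with post values, the planned rank-sum test ignores the pairing. Its actual level lies well below 0.05 for any clearly positive correlation: about 0.02 at r = 0.3, falling below 0.001 at r = 0.8. For a 0.5 SD change in 23 patients the power cost runs from about 13 percentage points at r = 0.3 (46% to 33%), through 29 at r = 0.5 (60% to 31%), to 52 at r = 0.7 (82% to 30%). It is smaller for larger changes or pooled arms.

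The direction rests only on the correlation being positive, which is to be expected for two recordings about a month apart in the same patients with medication changes prohibited. The sizes rest on the assumed correlation, change and normality. The sample size, the balance and cognitive outcomes and their ANOVA are untouched.

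**What to change.** In section 2.4, replace the rank-sum clause with two statements:

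1. Within each arm, the pre/post change in EEG entropy is described with the Wilcoxon signed-rank test on the paired values.
2. The arms are compared with the Mann–Whitney (rank-sum) test on each patient's post-minus-pre change, and this is the EEG comparison from which an effect of the intervention is judged.

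This settles both possible meanings of the present wording and ends the naming of one test under two names. The cost is one sentence in the analysis section, made before the EEG data are analysed. It needs no new data and no change to sample size or visits.
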